1. INVESTIGATIONAL PRODUCT

Details of the study product are presented in the following table:

| **Study Product** | **Product Code** | **Format** | **Product & Manufacturer** | **Nicotine Yield/Content** |
| --- | --- | --- | --- | --- |
| 1 | THP1.1(RT) | THP | Glo device with neostik, British American Tobacco | 0.68 mg/neostik^a^ |

^a^ nicotine yield under modified Health Canada Intense machine smoking regime; 55 mL puff volume; 30 second puff interval; 2 second puff duration; 8 puffs; no vent blocking.

The product is commercially available in Japan, Italy, Canada, Romania, South Korea, Russia, and Switzerland, and will be supplied by the Sponsor.

Prior to being distributed to subjects, study products will be kept in their packages and stored at room temperature under temperature monitored conditions. Subjects randomised to the THP arm will be provided with instructions for storage of the product. No special procedures are required for the safe handling of the products, other than ensuring that only the charger supplied with the THP is used to charge the device. All products must be kept out of sight and reach of children.

- 1. Identity of Investigational Products

Production lot number and date of manufacturing of the investigational products will be documented in the study file for products administered in Arm B.

The THP1.1(RT) THP device will be supplied by the Sponsor along with a micro-USB charger, a cleaning brush, and instructions for use. The device must only be charged as per the device instruction document.

Tobacco heating products, packs and cartons will be pre-labelled as per clinical sites standard operating procedures.

- 1. Accountability

Records will be maintained showing the receipt and disposition of the study supplies by the Investigator or their appropriately qualified designee. The Sponsor will be permitted at intervals and upon request during the study to check the supplies storage and assembly procedures and records at each clinical site.

Following completion of the clinical phase of the study and Sponsor review of accountability, the Investigator or their appropriately qualified designee will ensure that all unused supplies will either be returned to the Sponsor (together with the accountability records) or will be destroyed and Certificates of Destruction provided to the Sponsor, as directed by the Sponsor.

- 1. Blinding

This study will not be blinded.

- 1. Randomisation

Subjects in the continue-to-smoke/THP population will be randomised to Arm A or B. A randomisation scheme will be provided for the clinical sites. Each site will recruit a similar number of male and female subjects and a similar number of subjects ≤ 40 years old and > 40 years old at the time of randomisation.

Each site will receive 4 randomisation lists:

1. Males ≤ 40 years old.
2. Males > 40 years old.
3. Females ≤ 40 years old.
4. Females > 40 years old.

The allocation of subjects in each age/sex combination will be monitored on an ongoing basis during the study and if there is considered to be an imbalance between male and female subjects ≤ 40 years old and > 40 years old which could lead to problems when interpreting the data then the sites will be notified and will endeavour to prioritise the recruitment of subjects in the relevant category.

There will be no randomisation for subjects in the intend-to-quit population and never‑smoked populations; however, sites will endeavour to balance these populations in relation to male and female subjects and subjects ≤ 40 years old and > 40 years old.

- 1. Compliance

The study will be conducted in the ambulatory setting. Subjects will be required to comply with their randomised product or cessation aid, dependent on study arm, as indicated in Section 3.1.3.

Subjects will be instructed of the importance of complying with their randomised product (Arms A and B) or of not smoking cigarettes or using the THP (Arms D and E). Subjects will be asked to report any non-compliance via the automated eDiary (or paper diary if required) (Arms A, B and D) or using a paper diary (Arm E), and will be informed that compliance assessments will be conducted at selected clinic visits.

1. Selection of Study Population
   1. Selection of Study Population

Three populations will be recruited in total: 2 populations of smokers (Arms A, B, and D) and one population of subjects who have never smoked (Arm E).

For Arms A and B, 265 male or female subjects who have smoked 10 to 30 cigarettes per day, inclusive, commercially available and/or roll your own, non-menthol CPD, and who are willing to switch to a THP will be enrolled in this study. For Arm D, 190 male or female subjects who smoke 10 to 30, inclusive, commercially available and/or roll your own, non‑menthol CPD and who are intending to cease all non-medicinal nicotine use will be enrolled in this study. For these 2 populations, subjects will have smoked for at least 5 years consecutively. The subjects’ smoking status will be verified using a urinary cotinine test (cotinine >200 ng/mL) and an exhaled CO measurement (exhaled CO ≥ 7 ppm; subjects may be rescreened if CO levels are < 7 ppm).^19^

For Arm E, 40 subjects who have never smoked (< 100 cigarettes in their life and none within 30 days prior to Screening) will be recruited.

Each site will recruit a similar number of male and female subjects and a similar number of subjects ≤ 40 years old and > 40 years old, as described in Section 4.4.

- 1. Determination of Sample Size

A target of 50 completed subjects in each of the Arms A, B, and D has been set for this study. This is based on power for the primary objective of multiple between-arm comparisons. Calculations are based on the primary biomarker requiring the largest sample size (Augmentation Index [AIx]) between test and control products. Specifically, the power calculation was based on the number of subjects required to perform a contrast based on the F-statistic with 90% power between the arm using THP1 and the smoking arm at Day 360. The sample size was determined to be adequate based on AIx with expected means of 25.7 and 17. 5 for smoker and THP arms, and a common standard deviation of 12.4.^20^

This calculation assumes an 80% change with respect to that observed in subjects quitting smoking and an alpha level of 0.0451, adjusted for timepoint multiplicity using O’Brien‑Fleming sequential approach.

Thirty completed subjects in Arm E has been determined empirically; no formal statistical analysis of sample size has been performed.

- 1. Inclusion Criteria

Subjects will be required to satisfy all of the following criteria at the Screening Visit, unless otherwise stated:

All Subjects:

1. Subjects will be:
   1. males or non-pregnant, non-lactating females
   2. between 23 and 55 years of age, inclusive. Age verification will be performed by checking government issued identification (e.g. passport or driving licence) during Screening
2. Subjects will have a:
   1. body mass index (BMI) between 17.6 and 32.0 kg/m^2^, inclusive
   2. body weight exceeding 50 kg (males) or 40 kg (females)
3. Subjects will be in good health, as judged by the Investigator or their appropriately qualified designee based on:
   1. medical history
   2. physical examination
   3. vital signs assessment (blood pressure < 140 mmHg systolic)
   4. 12-lead ECG
   5. clinical laboratory evaluations
   6. lung function tests (Gold stage 1 is acceptable; see exclusion criterion 16)
4. Subjects will have given their written informed consent to participate in the study and will have agreed to abide by the study restrictions.
5. Subjects must demonstrate the ability to comprehend the Informed Consent Form (ICF), be able to communicate well with the Investigator or their appropriately qualified designee, understand and comply with the requirements of the study, and be judged suitable for the study in the opinion of the Investigator or their appropriately qualified designee.
6. Subjects will be willing to refrain from consuming alcohol within 24 hours prior to Screening and Check-in at each study visit, with the exception of the Follow-up Visit.
7. Subjects will be willing to refrain from consuming barbequed or chargrilled food, and avoid being in the presence of the barbequed or chargrilled food for 48 hours prior to Check-in at each study visit. Subjects will also be willing to avoid food containing poppy seeds for 3 days before both Screening and Check-in at each study visit.

Arms A, B, and D:

1. Subjects will be regular smokers of commercially manufactured filter cigarettes and/or roll your own cigarettes.
2. Subjects will have smoked for at least five consecutive years prior to Screening.
3. Subjects will typically smoke at least 10 and a maximum of 30 CPD and must have a urine cotinine level > 200 ng/mL and an exhaled breath CO level ≥ 7 ppm at Screening.
4. Subjects in Arm A who continue to smoke will be willing to use factory-manufactured non-mentholated cigarettes and/or roll your own cigarettes.
5. Subjects in Arm B will be willing to use the study product (THP) provided to them during the study.
6. Subjects in Arm D will be willing to abstain from smoking and using NGPs.

Arm E

1. Subjects will have never smoked (<100 cigarettes in their life and none within 30 days prior to Screening) and will continue to not smoke or use any form of tobacco or nicotine‑containing product (including THPs) for the duration of the study.
   1. Exclusion Criteria

Subjects will be excluded from the study if they satisfy any of the following criteria at the Screening Visit, unless otherwise stated:

All subjects

1. Male subjects who do not agree, or whose partners of childbearing potential do not agree, to use a barrier method of contraception (i.e. a condom with spermicide) or to refrain from donating sperm from Visit 1 until the end of the Follow-up Visit (see Section 7.1.7).
2. Female subjects of childbearing potential who do not agree to use a highly effective method of birth control in conjunction with male barrier method contraception (i.e. a condom with spermicide) from the time of signing the ICF until the end of the Follow-up Visit (see Section 7.1.7).
3. Female subjects who are pregnant or breastfeeding. This will be confirmed at Screening and Visit 1. Any female subject who becomes pregnant during this study will be withdrawn.
4. Subjects who have donated:
   1. ≥400 mL of blood within 12 weeks (male) or 16 weeks (female) prior to Visit 1.
   2. plasma in the 2 weeks prior to Visit 1.
   3. platelets in the 6 weeks prior to Visit 1.
5. Subjects who have an acute illness (e.g. upper respiratory tract infection) requiring treatment within 4 weeks prior to Visit 1 (subjects who had viral infections that resolved ≥2 weeks prior to Visit 1 will be admissible to this study).
6. Subjects who have a significant history of alcoholism or drug/chemical abuse within 24 months prior to Screening, as determined by the Investigator.
7. Subjects who have:
   1. a positive urine drugs of abuse screen (confirmed by repeat) at Screening or Visit 1.
   2. a positive alcohol breath test (confirmed by repeat) at Screening or Visit 1.
8. Subjects who:
   1. are carriers of the hepatitis B surface antigen (HBsAg).
   2. are carriers of the hepatitis C antibody.
   3. have a positive result for the test for human immunodeficiency virus (HIV) antibodies.
9. Subjects who have used prescription or over-the-counter (OTC) bronchodilator medication (e.g. inhaled or oral β-adrenergic agonists) to treat a chronic condition within the 12 months prior to Visit 1.
10. Subjects who have received any medications or substances (other than tobacco) which
    1. interfere with the cyclooxygenase pathway (e.g. anti-inflammatory drugs including aspirin and ibuprofen) within 14 days prior to Visit 1.
    2. are known to be strong inducers or inhibitors of cytochrome P450 (CYP) enzymes within 14 days or 5 half-lives of the drug (whichever is longer) prior to Visit 1.
11. Subjects who perform strenuous physical activity (exceeding the subject’s normal activity levels) within 7 days prior to Screening or Visit 1.
12. Subjects who are unable to communicate effectively with the Investigator/study staff (i.e. language problem, poor mental development, or impaired cerebral function).
13. Subjects who are unwilling or unable to comply with the study restrictions and requirements.
14. Employees and immediate relatives of the tobacco industry and the clinical site.
15. Subjects who are still participating in another clinical study (e.g. attending follow-up visits) or who have participated in a clinical study involving administration of an investigational drug (new chemical entity) in the past 3 months prior to first product use.
16. Subjects who have any clinically relevant abnormal findings on the physical examination, medical history, ECG, lung function tests (post-bronchodilator FEV_1_/FVC < 0.7 and FEV_1_ < 80% predicted value at post-bronchodilator spirometry or have an asthma condition [post-bronchodilator FEV_1_/FVC < 0.75 and reversibility in FEV_1R_ > 12% and > 200 mL from pre- to post-bronchodilator values at Screening]) or clinical laboratory panel, unless deemed not clinically significant by the Investigator or their appropriately qualified designee.
17. Subjects who have, or who have a history of, any clinically significant neurological, gastrointestinal, renal, hepatic, cardiovascular, psychiatric, respiratory, metabolic, endocrine, haematological or other major disorder that, in the opinion of the Investigator or their appropriately qualified designee, would jeopardise the safety of the subject or impact on the validity of the study results.
18. Subjects who have previously been diagnosed with any form of malignancy.
19. Subjects who have any clinically significant abnormal laboratory safety findings at Screening, as determined by the Investigator or their appropriately qualified designee (1 repeat assessment is acceptable).
20. Subjects who have previously been enrolled in or withdrawn from this study.
21. Subjects who, in the opinion of the Investigator, should not participate in this study.

Arms A, B, and D:

1. Subjects who regularly use any nicotine or tobacco product other than commercially manufactured filter cigarettes and/or roll your own cigarettes within 14 days of Screening.

Arms A and B:

1. Subjects who are self-reported non-inhalers (smokers who draw smoke from the cigarette into the mouth and throat but who do not inhale).
2. Subjects who, prior to randomisation, are planning to quit smoking in the next 12 months. All subjects will be informed that they are free to quit smoking and withdraw from the study at any time. Any subject who decides to quit smoking will be directed to appropriate stop smoking services (Section 3.4).
3. STUDY ACTIVITIES

A detailed Schedule of Assessments can be found in Appendix 15.1.

- 1. Screening
     1. Screening Visit

Subjects will attend a Screening Visit within 28 days prior to Visit 1. Prior to the Screening Visit, subjects will:

- refrain from strenuous physical activity (exceeding the subject’s normal activity levels) for 7 days.
- abstain from alcohol for 24 hours.

Subjects will be asked to sign the study‑specific ICF in the presence of a suitably trained clinical site operations staff member prior to any screening procedures being performed. The information recorded for all subjects, regardless of their suitability for the study, will be retained and archived in accordance with the Investigator’s data retention policies. All assessments conducted at the Screening Visit are presented in the Schedule of Assessments (Appendix 15.1).

All subjects in the continue-to-smoke/THP population will be shown the THP1.1(RT) THP products at Screening.

Subjects in Arm D (smoking cessation) who have passed all screening assessments and signed the ICF will be contacted prior to Visit 1 to discuss their smoking cessation strategy. Contact may take the form of a telephone call or site visit.

- - 1. Re-screening

Subjects who undergo screening but who are not enrolled will be eligible for re-screening at the discretion of the Investigator.

- 1. Visit 1

Prior to Check-in, all subjects will:

- Refrain from strenuous physical activity (exercise exceeding the subject’s normal activity levels) for 7 days.
- Abstain from alcohol for 24 hours.
- Adhere to dietary restrictions detailed in Section 7.1.3.
- Collect a 24-hour urine sample (to begin on Day -1 [AM] and to include the first void of the day on Day 1).

At Visit 1, all subjects will undergo the following demographic and safety assessments prior to randomisation (Arms A and B) or enrolment (Arms D and E):

- Review of inclusion/exclusion criteria
- Review of medical history
- Physical examination (symptom driven)
- Vital signs
- Resting 12-lead ECG
- Lung function test
- Urine drugs of abuse screen
- Urine cotinine test
- Alcohol breath test
- Review of AEs/SAEs
- Review of concomitant medication
- Clinical laboratory evaluations (the Investigator is not required to review these data before randomisation or enrolment).

For female subjects:

- Urine pregnancy test

Following randomisation (Arms A and B) or enrolment (Arms D and E), subjects will undergo the following baseline assessments:

- Blood sampling for primary endpoint biomarkers, BoE, BoBE, and exploratory endpoints
- Nasal transcriptomics sampling
- Carbon monoxide and NO breath tests
- Physiological endpoint assessments (body weight/waist circumference, carotid/femoral pulse wave velocity, 6-minute walking test, finger plethysmography)
- Questionnaire administration
  - 1. Continue-to-Smoke/Next Generation Product Population Only

Following safety assessments but prior to randomisation, product use training and demonstration will occur for subjects in the continue-to-smoke/THP population. Subjects will be offered the opportunity to trial up to 2 THP sticks. Product use will be separated by a minimum of 15 minutes during which subjects will not be allowed to use any nicotine‑containing products. The purpose of the product test is to allow subjects to experience the THP that they could be randomised to. If subjects decide that they do not wish to continue in the study following the product test, they will be withdrawn prior to randomisation. Subjects will be informed that there is an approximate 24.5% chance of being asked to continue to smoke their own brand cigarettes, and a 75.5% chance of being asked to smoke the THP.

Following the product test, subjects willing to take part in the trial will be randomised as described in Section 4.4. An additional, more detailed product use training and demonstration may be performed after randomisation, which may include, but may not be limited to, a demonstration of cleaning and storage instructions.

Prior to Check-out on Day 1, subjects randomised to Arm B will be provided with the investigational product.

Following randomisation, subjects will be instructed to use only their assigned product. As non-compliance with the study products may occur, there will be a 14 day transition period following Visit 1 where non-compliance is tolerated. After this period, subject non‑compliance will be assessed on an individual basis, and may lead to subject withdrawal as described in Section 3.3.

- - 1. Intend-to-quit Population

Subjects in the intend-to-quit population will be expected to refrain from nicotine-containing product use from the time of enrolment at Visit 1. Subjects will receive smoking cessation support as described in Section 3.4.2. It is anticipated that subjects may not stop using all tobacco products immediately following enrolment, the so the use of tobacco products will be tolerated during a 14 day transition period following Visit 1. After this period, use of tobacco products by a subject will be assessed on an individual basis, and may lead to subject withdrawal as described in Section 3.3.

- - 1. Never-smoked Population

Subjects in the never-smoked population (Arm E) will be instructed not to use tobacco or nicotine products for the duration of the study.

- 1. Visit 2 to Visit 13

Subjects in Arms A, B, and D will return to the clinic for non-residential visits every 30 days (+/-3 days for Visit 2 to Visit 4, +/- 2 weeks for Visit 5 to Visit 13). Subjects in Arm E will return to the clinic for non-residential Visit 4 (Day 90 +/- 3 days), Visit 7 (Day 180 +/- 14 days), and Visit 13 (Day 360 +/- 14 days).

Prior to Check-in at each visit, subjects will:

- Refrain from strenuous physical activity (exercise exceeding the subject’s normal activity levels) for 7 days.
- Abstain from alcohol for 24 hours.
- Adhere to dietary restrictions detailed in Section 7.1.3.
- Provide a 24-hour urine collection sample (to begin the day [AM] prior to Check-in for Visits 2, 3, 4, 7, 10, and 13 only).

Following Check-in, subjects will undergo the following assessments:

- Urine drugs of abuse screen
- Alcohol breath test

For female subjects:

- Urine pregnancy test

The following samples/assessments will be completed at the visits indicated in the Schedule of Assessments (Appendix 15.1):

- Blood sampling for BoE, BoBE, and exploratory endpoints
- Nasal transcriptomics sampling
- White blood cell transcriptomics sampling
- End of 24-hour urine collection
- Carbon monoxide and NO breath tests
- Physiological endpoint assessments (body weight/waist circumference, carotid/femoral pulse wave velocity, 6-minute walking test, finger plethysmography)
- Questionnaire administration
- Safety assessments

For subjects in Arm B, an assessment of product usage should be undertaken, and the allocation of product should be 120% of the product used in the previous period, up to a limit of 200%. At these visits, subjects will return all empty, part-used, and unused packs of THP consumables. At Visit 13, subjects will return all empty, part-used, and unused packs of THP consumables, and the study devices, charger, and other accessories supplied to them for this study.

- 1. Follow-up Contact
     1. Visits 1 to 12

All subjects in Arms B and D will be contacted by telephone 7 to 14 days after Visit 1 to aid randomised product (Arm B) or smoking cessation (Arm D) compliance. Subjects will be reminded of the support available (see Section 3.4), and will be able to speak to an appropriately trained member of staff to help to prevent combustible cigarette use.

At the discretion of the Investigator or their appropriately trained designee, additional telephone calls or clinical site visits may be scheduled for subjects in Arm D to monitor or update their smoking cessation strategy or prescriptions.

- - 1. Visit 13

All subjects will return to the site for a Follow-up assessment within 28 days after Check-out at Visit 13. The Investigator or their appropriately qualified designee will complete the following safety assessments:

- Physical examination (symptom driven)
- Vital signs
- 12-lead ECG
- Review of AEs/SAEs
- Clinical laboratory evaluations
- Review of concomitant medication.

For female subjects:

- Urine pregnancy test.

Provided there are no AEs which require further attention, the subject’s participation in the study will be complete. A further visit may be scheduled if deemed necessary by the Investigator or their appropriately qualified designee.

Subjects who, after enrolment, discontinue the trial prematurely should be encouraged to participate in this follow-up procedure. If their withdrawal is due to safety evaluations then the subjects should be followed until these return to baseline levels or until the Investigator or their appropriately qualified designee has determined that these events are no longer clinically significant.

Subjects who develop an AE at any time during the study will be followed until any required evaluations have returned to baseline or until the Investigator or their appropriately qualified designee has determined that these events are no longer clinically significant.

Reported AEs will be followed until resolution whenever possible.

- 1. Study Termination

The study may be discontinued at the discretion of the Investigator (or designee), Sponsor, or Sponsor’s Medical Monitor if any of the following criteria are met:

- adverse events unknown to date
- increased frequency, severity, and/or duration of known, anticipated, or previously reported AEs (this may also apply to AEs defined at Check‑in as baseline signs and symptoms)
- At Day 90, <25 subjects observe reductions ≥50% from baseline for at least 2 of the following biomarkers of exposure: CEMA, S-PMA, 2-AN
- medical or ethical reasons affecting the continued performance of the study
- difficulties in the recruitment of subjects
- administrative reasons
- cancellation of product development.

A written statement fully documenting the reasons for study termination will be provided to the ethics committee (EC).

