**LIST OF FIGURES**

[Figure 1: Study Schematic 34](#_Toc503183717)

LIST OF ABBREVIATIONS

| AE | adverse event |
| --- | --- |
| AIx | Augmentation Index |
| BAT | British American Tobacco (Investments) Ltd. |
| BMI | body mass index |
| BoBE | biomarker of biological effect |
| BoE | biomarker of exposure |
| CO | carbon monoxide |
| CPD | cigarettes per day |
| CRU | Clinical Research Unit |
| CTA | Clinical Trial Authorisation |
| CYP | cytochrome P450 |
| EC | ethics committee |
| ECG | electrocardiogram |
| eCRF | electronic Case Report Form |
| FDA | Food and Drug Administration |
| FEV_1_ | forced expiratory volume in 1 second |
| FTCD | Fagerström test for cigarette dependence |
| FVC | forced vital capacity |
| IB | Investigator’s Brochure |
| ICF | Informed Consent Form |
| ICH | International Council for Harmonisation |
| ITT | intent-to-treat population |
| LED | light-emitting diode |
| MHRA | Medicines and Healthcare products Regulatory Agency |
| MRTP | modified risk tobacco product |
| NGP | Next Generation Product |
| NO | nitric oxide |
| NRT | nicotine replacement therapy |
| OTC | over-the-counter |
| PP | per-protocol population |
| QTcF | QT interval corrected for heart rate using Fridericia’s method |
| SAE | serious adverse event |
| THP | tobacco heating product |
| VAS | visual analog scale |
| WBC | white blood cell |
| WHO | World Health Organisation |

DEFINITION OF TERMS

| Baseline assessments | Assessments that occur before the product test on Day 1 |
| --- | --- |
| Concomitant medication | Concomitant medication refers to all medication taken during the study conduct period from the Informed Consent Form (ICF) signature onwards. Medications started prior to signing of the ICF but which the subject continued to take during the study, were considered to be concomitant medications. |
| Conventional cigarette | Conventional cigarette refers to commercially available manufactured cigarettes, and excludes other tobacco products including hand-rolled cigarettes, cigars, pipes and bidis. |
| Enrolled not randomised | Any subject in Arms A or B who is enrolled onto the study on Day 1 but who withdraws or is withdrawn prior to randomisation. |
| Exposure period | From start of randomised product use (Arms A or B) on Day 1 until Check‑out from the clinic on Day 360. |
| Follow-up | Follow-up Visit will occur within 28 days following Check-out on Day 360. |

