Subjects will be fasted, will avoid caffeine (Section 7.1.3), and will not smoke (Arms A, B, and D) for 2 hours prior to collection of blood samples.

The exact volumes of each sample may change but the total volume of blood drawn for any subject will not exceed 400 mL.

- 1. Other Study Assessments
     1. Physiological Assessments
        1. Body Weight and Waist Circumference

Body weight in underclothing and without shoes and waist circumference will be measured at the timepoints indicated in the Schedule of Assessments (Appendix 15.1).

- - - 1. Augmentation Index and Carotid/Femoral Pulse Wave Velocity

Augmentation index and carotid/femoral pulse wave velocity assessments will be conducted at the timepoints indicated in the Schedule of Assessments (Appendix 15.1) using a SphygmoCor XCEL device according to the manufacturer’s instructions.

Prior to measurements, subjects will fast and avoid caffeine for 4 hours (described in Section 7.1.3, and will not smoke (Arms A and B) for 2 hours. Subjects will have rested for 10 minutes in a supine position prior to measurements.

- - - 1. 6-minute Walking Test

A 6-minute walking test will be conducted at the timepoints indicated in the Schedule of Assessments (Appendix 15.1) in accordance with the European Respiratory Society/American Thoracic Society guidelines.^23^

Subjects will be asked to walk the greatest distance they can in 6-minutes without jogging or running. Subjects will be instructed to wear appropriate clothing, and will be monitored throughout the test by a suitably qualified member of staff. Subjects are permitted to eat a light meal prior to the test occurring, and will be required to rest in a seated position for 10 minutes prior to the start of the test. During the test, subjects will regulate their pace, and can slow down or stop if required. Subjects blood oxygen saturation levels (SpO_2_) will be monitored continually during the 6-minute walking test using a wrist-mounted pulse oximeter.

- - - 1. Finger Plethysmography

Finger plethysmography will be conducted at the timepoints indicated in the Schedule of Assessments (Appendix 15.1) using an EndoPAT^TM^ device and software according to the manufacturer’s instructions.

Subjects will be fasted, will avoid caffeine (Section 7.1.3), and will not smoke (Arms A, B, and D) for at least 2 hours prior to measurements. Subjects will have rested for 10 minutes in a supine position prior to measurements.

- - 1. Questionnaires

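### For Arms A and B the protocol defines baseline as before the Day 1 product test, but the Visit 1 flow places most baseline endpoint assessments after that test and after open-label randomisation

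*Protocol*

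**What the plan says.** The Definition of Terms describes baseline assessments as "Assessments that occur before the product test on Day 1".

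Section 6.2 (Visit 1) lists demographic and safety assessments to be done before randomisation or enrolment. It then states: "Following randomisation (Arms A and B) or enrolment (Arms D and E), subjects will undergo the following baseline assessments". The list that follows contains endpoint blood samples, nasal sampling, CO and NO breath tests, physiological assessments and questionnaires. The physiological entry reads "Physiological endpoint assessments (body weight/waist circumference, carotid/femoral pulse wave velocity, 6-minute walking test, finger plethysmography". AIx is not named there, although the Schedule of Assessments (Appendix 15.1) marks it at Visit 1 (Baseline) under physiological endpoints.

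Section 6.2.1 fixes the place of the product test: "Following safety assessments but prior to randomisation, product use training and demonstration will occur for subjects in the continue-to-smoke/THP population". On exposure it says "Subjects will be offered the opportunity to trial up to 2 THP sticks". On sequence it says "Following the product test, subjects willing to take part in the trial will be randomised as described in Section 4.4".

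Three other statements matter. The study is not blinded (Section 4.3). The primary contrasts come from models adjusted for baseline (Section 9.3). Before AIx and pulse wave velocity, subjects "will not smoke (Arms A and B) for 2 hours" (Section 7.5.1.2).

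**The concern.** The definition and the visit flow give opposite orders for the same measurements. The baseline value is the covariate in the primary and secondary models, so its timing should be fixed and the same at every site. In a multi-centre study, two incompatible instructions invite sites to settle the matter differently.

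There are two separate consequences:

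- **Product test before baseline.** Some Arm A and B subjects may be measured after using THP sticks. Arms D and E have no product test. Baseline conditions may therefore differ between A/B and D/E, which bears on the secondary comparisons of Arm B with Arms D and E.
- **Randomisation before baseline.** Subjects and staff know the allocation when baseline is taken. A baseline that responds to that knowledge is no longer a pre-randomisation covariate, and adjusting for it can bias A versus B. Subjective or effort-dependent measures (questionnaires, the 6-minute walk) are most open to this.

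**Working it through.** **Step 1. Put the order together for Arms A and B.**

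| Source | Order stated |
|---|---|
| Definition of Terms | baseline, then product test |
| Section 6.2.1 | safety assessments, then product test, then randomisation |
| Section 6.2 | safety assessments, then randomisation, then baseline |

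The last two rows combine to: safety assessments, product test, randomisation, baseline. This contradicts the first row.

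**Step 2. Sort the Visit 1 measurements.**

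- Before the product test: the 24-hour urine, which runs from Day -1 to the first void of Day 1 and supplies Total NNAL and 8-Epi-PGF2α; vital signs; ECG; spirometry; and clinical laboratory tests. By note 1 to the blood-volume table in Section 7.4.2, the last group includes glucose, total cholesterol and triglycerides.
- After randomisation as written: the other endpoint blood samples, nasal sampling, CO/NO, physiological measures and questionnaires. AIx belongs here only by inference from the Schedule.

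Two of the three primary endpoints are therefore unaffected.

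**Step 3. Reproduce the planned sample size (Section 5.2).** Inputs: AIx means 25.7 and 17.5 (difference 8.2), SD 12.4, alpha 0.0451 (two-sided assumed), power 90%.

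n per arm = 2 × (2.004 + 1.282)² × 12.4² / 8.2² = 49.4, rounded up to 50. This matches the plan. Power at 50 per arm is 0.904 by the normal approximation and 0.898 by the noncentral F with 1 and 98 df. The calculation uses the raw SD and no baseline correlation, so the timing of baseline does not enter it.

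**Step 4. Effect of the trial sticks on A versus B.** They come before randomisation and are offered to both arms, so any shift is equal in expectation. What remains is noise. With baseline to Day 360 correlation r and added baseline variance v (as a fraction of 12.4²), the correlation becomes r/√(1+v) and the residual SD is 12.4 × √(1 − r²/(1+v)). The protocol gives neither r nor v; both are assumed.

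| r | Power, v = 0 | Power, v = 0.5 |
|---|---|---|
| 0.3 | 0.928 | 0.920 |
| 0.5 | 0.965 | 0.947 |
| 0.7 | 0.996 | 0.979 |

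All values stay above 90%.

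**Step 5. Effect if knowledge of the arm shifted baseline AIx (illustration only).** Bias = slope × arm-specific shift. SE = 12.4 × √(1 − slope²) × √(2/50), taking equal variances at both times so that slope equals correlation. For example, slope 0.5 and a shift of 2 points give a bias of 1.0, an SE of 2.15 and a type I error of 0.069 against the nominal 0.0451. Over slopes of 0.3 to 0.7 and shifts of 1 to 3 points, the bias is 0.3 to 2.1 points (4% to 26% of 8.2) and the type I error is about 0.047 to 0.207. The protocol does not show that any such shift occurs.

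**The case against.** The strongest reply is that this is a drafting conflict with little consequence for the primary test. Much of that stands.

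- **Contaminated AIx covariate.** A reader might infer that the powered endpoint's baseline is contaminated by THP nicotine. The protocol does not show this. Use of the sticks is optional, so not all 265 planned Arm A/B subjects need be exposed. AIx is not named in the post-randomisation list.
- **Breach of the 2-hour rule.** A reader might infer that the flow breaks the abstinence rule before vascular measures. Sections 6.2 and 6.2.1 give an order but no clock times, so a wait is compatible with them. The narrower gap is that Section 7.5.1.2 speaks of smoking and does not name THP use, whereas Section 7.3.1 names study products as well as cigarettes in its 30-minute rule before CO and NO. Section 6.2.1 itself speaks of smoking the THP, so the intended reach is unclear.
- **Lost sample size.** If r were assumed to fall from 0.6 to 0.5, the residual SD would rise from 12.4 × √0.64 = 9.92 to 12.4 × √0.75 = 10.74, an equivalent sample of 0.64/0.75 = 85%. That drop is invented, and both values are below the 12.4 used for planning. The loss is from a gain the plan never counted.
- **Nicotine-free comparison arms.** Arm D subjects smoke their usual brand until enrolment (Section 3.1.3), so their baseline is not nicotine-free either.
- **Open-label effect on AIx.** AIx is measured by device in a rested, supine subject, and no mechanism for an allocation effect is documented.

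None of this reconciles the two orders, and none of it answers the open-label point for questionnaires and the walk test.

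**Conclusion.** The contradiction is established from the text alone: for Arms A and B, following Section 6.2 as written breaks the protocol's own definition of baseline. The trial sticks can add noise to the A versus B covariate but not bias. They may make Arm A/B baselines differ from those of Arms D and E, by an amount and in a direction the protocol does not allow one to state. The risk to A versus B is baseline taken after open-label allocation, chiefly for questionnaires and the walk test, which are secondary endpoints.

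For AIx the size is unknown. The range in Step 5 rests on assumed slopes and shifts and shows only what would follow if a shift existed. Total NNAL and 8-Epi-PGF2α are untouched, and 50 per arm with the stated power holds.

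**What to change.** Amend Sections 6.2 and 6.2.1 so that all baseline endpoint assessments are completed before the product test and before randomisation, in line with the Definition of Terms. Name AIx in the Visit 1 list. Reconcile Section 7.5.1.2 with Sections 6.2.1 and 7.3.1 so that it is clear whether the 2-hour no-smoking wording covers THP use.

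For subjects already enrolled, record for each baseline measurement whether it was taken before or after the product test and randomisation. Run a sensitivity analysis on that flag, for example by adjusting for it. Dropping the flagged subjects is not advisable: if sites followed the written flow, that could remove most of Arms A and B.

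The cost is a re-ordered visit and some baseline tests done on subjects who then decline after the product test. Subjects before and after the amendment would also have baselines taken under different conditions, which the flag lets the analysis examine.
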